**INTERVENTION:** The trial is comparing two active task-shifting implementation models of depression care: a *protocolized model* in which care is provided largely by trained nurses who act as depression care managers, and a model that relies on the *clinical acumen* of trained primary care providers (most, but not all, of whom are nurses as well). An alternative approach to the use of a structured protocol to guide depression care by non-mental health professionals, the clinical acumen model (like the protocolized model) takes an active approach to depression care by integrating a brief routine depression screening process for all patients at each clinic visit, but what the primary care provider does with this screening information is up to their discretion as opposed to following a structured protocol.

**PRIMARY OBJECTIVES:** The objectives of INDEPTH-Uganda are to compare the two task-shifting models on (1) reach (screening and follow-up rates), adoption (treatment uptake), fidelity (quality of depression care implementation by the providers), and effectiveness (alleviation of depression symptoms) implementation parameters. A secondary objective is to assess the impact of depression treatment on key economic (work) and public health (ART adherence, condom use) outcomes.

**IRB approval:** The study protocol has been approved by Institutional Review Boards at RAND Corporation (protocol # 2012-0115), Mildmay Uganda, and the Uganda National Council for Science and Technology.

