## 1.0 INTRODUCTION

In response to the NIH/PEPFAR RFA for implementation science and impact evaluation, this proposal addresses these priority areas: integration of HIV primary care and a common co-morbidity (depression), and examining depression treatment as a means to promote HIV care adherence and prevention of transmission. Sub-Saharan Africa (SSA) has undergone dramatic scale-up of HIV care and antiretroviral therapy (ART), with over 3 million on treatment in the region. The ultimate goal of HIV care is not only prolonged health and survival, but to provide a functioning level that enables clients to work, provide for their families, and prevent transmission of the virus to others. In fact, ART has led to dramatic reductions in mortality and morbidity, reduced infectiousness, and increased work productivity. However, our research in Uganda reveals depression to be a key threat to these critical public health benefits of HIV treatment. In our prospective cohort study that observed clients over the first year of care, multivariate analysis revealed depression to be the key impediment to ART adherence, whether or not someone was able to work, and consistent condom use.

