## 2.0 STUDY OBJECTIVES

### Primary Aims:

1. Compare the task-shifting (nurse) vs. standard (physician) models on the following quality of care indicators:  
(a) depression treatment uptake, and (b) reduced depression (treatment response). *Hypothesis: Task-shifting model is associated with greater treatment uptake and depression reduction compared to standard model.*
2. Examine the relationship between change in depression and key economic and public health outcomes. *Hypothesis: Reduced depression is associated with better ART adherence, working, and more condom use.*

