## 6.0 INTERVENTION: Task-Shifting Depression Care Models

### 6.1 Protocolized Model

Drawing from collaborative care models of depression treatment such as Partners in Care, MANAS and STAR\*D, the protocolized model implements an algorithm-based, nurse-driven approach to administering depression diagnosis and antidepressant therapy. While other collaborative care models incorporate psychotherapy and reserve antidepressants for severe depression, our model focuses solely on the use of antidepressants. We believe that use of medication requires relatively less trained resources and personnel time than would be needed to add a form of psychotherapy, resulting in a more reliable and scalable treatment for resource constrained settings. The components of the protocolized model are outlined below and summarized (in comparison with the clinical acumen model) in Table 1.

***Routine depression screening:*** All adult clinic patients will be screened for depression at each clinic visit using the first two items of the Patient Health Questionnaire (PHQ-2), administered at the triage station (along with measurements of body weight, blood pressure, pulse and elicitation of presenting health problems) by expert clients or VHT workers. The PHQ-2 assesses depressed mood and loss of interest; patients who screen positive for depression (3+ scores; range: 0-6) will be referred to the nurse in the protocolized model for further depression evaluation if medically stable; in the clinical acumen model, PHQ-2 data are relayed to the primary care provider. Medical stability is defined as not about to start (or recently started) ART or treatment for an acute opportunistic infection (see Figure 1). Further evaluation is deferred for medically unstable patients until their condition and treatment is stable, as mood may improve once they are medically stable, and starting antidepressants simultaneously with other medical treatments would complicate side effect and response evaluation. However, depressed patients who are medically unstable will be evaluated for suicide risk and the need for immediate treatment.

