**AIM 2: Assess relationship of depression and public health and economic outcomes:** We will first examine correlates of baseline depression (PHQ-9) including ART adherence, condom use, and work activity. Multi-variate analysis will take advantage of repeated observations per individual to model the effect of changes in depression on changes in these outcomes (individual fixed effects), controlling for unmeasured individual characteristics that may affect both depression and the outcomes. However, it does not control for simultaneity (e.g., change in work status leads to lower depression). With 3 time-points, instrumental variables approaches combined with fixed effects potentially can deal with this problem, using baseline depression to predict change in depression from month 6 to 12, if baseline depression is strongly correlated with change in depression over time. The fixed effects model will also indicate important time patterns in depression and the other outcomes.

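### Aim 2 credits individual fixed effects with more confounding control than they give: ART starts and illness during follow-up can still bias the depression–work association

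*Protocol*

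**What the plan says.** Section 9.2 (Aim 2) uses the three assessments per patient "to model the effect of changes in depression on changes in these outcomes (individual fixed effects") and says this works by "controlling for unmeasured individual characteristics that may affect both depression and the outcomes". One limitation follows: simultaneity, for example a change in work status altering mood. As a possible remedy it offers instrumental variables, "using baseline depression to predict change in depression from month 6 to 12", on condition that the two are strongly correlated. The Aim 2 text names no time-varying health variable and does not mention study arm.

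The purpose of the analysis is worded in two ways:
- Study Overview: "A secondary objective is to assess the impact of depression treatment on key economic (work) and public health (ART adherence, condom use) outcomes".
- Section 2.0, under Primary Aims: "Examine the relationship between change in depression and key economic and public health outcomes", with the hypothesis "Reduced depression is associated with better ART adherence, working, and more condom use".

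Two statements elsewhere bear on confounding. Section 6.1 defers depression evaluation in medically unstable patients because "mood may improve once they are medically stable". Section 1.0 states that "ART has led to dramatic reductions in mortality and morbidity, reduced infectiousness, and increased work productivity".

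**The concern.** The statement about fixed effects has no limit to time-constant characteristics. Because simultaneity is the only problem conceded, a reader will take confounding to be dealt with. It is not. Anything that changes between visits and moves both PHQ-9 and the outcome stays in the estimate, and the protocol describes such a factor for work.

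Take a patient who starts ART at month 3, feels better and goes back to work. In this model that patient counts as evidence that less depression improves working. Aim 2 is meant to support the case that treating depression protects the economic and public health gains of HIV care, so part of the HIV course could be reported as a benefit of reduced depression.

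**Working it through.** **Can the confounder arise within follow-up?** Sections 5.0 and 6.1 require medical stability at entry, which excludes imminent or recent ART start and treatment of an acute opportunistic infection. Section 8.0 asks about ART adherence only where applicable, so some participants are not on ART. ART starts and new illness after enrolment therefore remain possible between the visits at baseline, month 6 and month 12 (7.0).

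**Which outcomes?** The documents supply both links for work: medical course to mood (6.1) and ART to work productivity (1.0). They do not for the other two. A patient who starts ART during follow-up has no baseline ART adherence from which to compute a change, and no mechanism is given for condom use.

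**Is there a stated figure to reproduce?** No. The protocol gives no power or effect figure for Aim 2.

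**Illustration 1: algebra, no true effect of depression on work.**

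Inputs from the protocol: up to 1500 patients with 10% attrition, so n = 1500 × 0.9 = 1350; SD 3.9 for PHQ-9 (9.1, Aim 1b), taken here as the SD of change. Assumed: SD of change in working 0.5; a share p starts ART or has a health change that shifts PHQ-9 by d and working by w.

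- Spurious slope = p(1−p) × d × w / 3.9²
- SE = 0.5 / (3.9 × √1350) = 0.0035, ignoring clinic clustering

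| p | d (PHQ-9) | w (working) | Slope per PHQ-9 point | Credited to a 5-point fall | z | False-positive rate |
|---|---|---|---|---|---|---|
| 10% | −2 | +0.15 | −0.0018 | 0.9 points | 0.51 | 8% |
| 20% | −2 | +0.15 | −0.0032 | 1.6 points | 0.90 | 15% |
| 20% | −3 | +0.20 | −0.0063 | 3.2 points | 1.81 | 44% |
| 30% | −4 | +0.25 | −0.0138 | 6.9 points | 3.96 | 98% |

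Example, second row: 0.2 × 0.8 × (−2) × 0.15 / 15.21 = −0.0032. With n = 1000 × 0.9 = 900 the rates are 7%, 11%, 31% and 90%. As a correlation between the two changes (slope × 3.9/0.5), the third row is only about −0.05 and the fourth about −0.11. In a cohort this large a weak shared cause is enough.

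**Illustration 2: simulation of the fixed-effects model.** Three visits, 400 runs per setting, true effect zero, a time-constant confounder always present. A health course with between-visit correlation 0.5 explains an assumed share of the within-person variance of both depression and outcome.

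| Share | Mean fixed-effects estimate, n = 1350 (SD per SD) | False positives, n = 1350 | False positives, n = 900 |
|---|---|---|---|
| 0% | 0.00 | 5% | 6% |
| 5% | −0.03 | 31% | 26% |
| 10% | −0.06 | 87% | 73% |
| 20% | −0.13 | 100% | 100% |
| 30% | −0.20 | 100% | 100% |

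At 0% the pooled regression gives −0.50 and fixed effects give 0.00, so fixed effects do what they can: they remove the constant confounder. Entering the health variable returns the estimate to about zero and the rejection rate to 4–6%. That assumes it is measured without error at each visit.

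**The case against.** **The plan is already cautious.** It concedes simultaneity, and section 2.0 words Aim 2 as an association. A reader might infer that the objective cannot be answered. The documents do not support that: the association in section 2.0 can be estimated, and only the Overview's claim about the impact of treatment goes beyond the analysis.

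**Covariate lists belong in the SAP.** That is fair, and an unlisted covariate alone would be no finding. What stands is what the protocol does state: an unrestricted claim for fixed effects, followed by a single conceded limitation.

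**The arms may be used.** Section 9.2 promises clinic-level t-tests first for most outcomes, which may cover work, adherence and condom use. So it would be wrong to say that the randomisation is never used for them. They are simply not named.

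**The confounder is narrow.** The entry rule largely removes recovery from an unstable state at baseline. This stands and limits the point to events during follow-up.

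**The instrument.** A reader might infer that baseline PHQ-9 has zero correlation with the month 6–12 change, because the Aim 1b model has an individual effect plus idiosyncratic error. But that text allows errors correlated over time, and the protocol makes the step conditional on a strong correlation. With an assumed 6-month autocorrelation r of 0.3–0.5 and between-person share c of 0.3–0.7, the correlation (1−c)(r²−r)/√(2(1−c)(1−r)) runs from about −0.10 to −0.21, a first-stage F of about 13 to 62 at n = 1350. The simulation, under different assumptions, gave median F of about 0.5 to 2.5. The strength is therefore an empirical question.

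Nor is the randomised arm a better instrument. At the protocol's own detectable difference (1.26 points, ICC 0.025, 135 per clinic), SE = 3.9 × √(2 × 4.35/675) = 0.443, so t = 2.85 and F is about 8, on 10 clinics. The arm could also affect adherence through its visit schedule rather than through depression.

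**Conclusion.** The point holds for the depression–work association. Section 9.2 overstates what fixed effects control, and the protocol itself describes a time-varying factor that can move both mood and work. The direction of the bias favours the Aim 2 hypothesis.

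The size is unknown. The documents give neither the share of participants not on ART nor the effect of an ART start or illness on PHQ-9 or work. The assumed scenarios run from near nominal error (8%) to almost certain false positives (98%), and the upper end needs a large share affected and large shifts. The illustrations show that the bias can matter at this sample size, not that it will.

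Separately, the Overview and section 2.0 differ in target (impact of treatment against association with change in depression) and in rank (secondary against primary). A reader might infer that comparing the arms would give the impact of treatment. It would not: both arms are active (1.0), so it gives one care model against the other.

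**What to change.** In section 9.2, Aim 2:

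1. State that individual fixed effects control for time-constant characteristics only. Add, as time-varying covariates from the chart data, ART status or start and new WHO stage 3–4 or opportunistic illness. Report results with and without them. Use MOS-HIV physical function only in a sensitivity analysis, because it may lie on the path from depression to work.
2. Name a between-arm intention-to-treat comparison of work, ART adherence and condom use, with the same clinic-level inference as Aim 1, interpreted as care model against care model.
3. Describe the fixed-effects result as an association, and reconcile the Study Overview with section 2.0 on both wording and rank.

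Cost: mostly wording, since these variables are already planned. Section 8.0 does not say when charts are abstracted, so abstraction must cover each wave. The arm comparison will have wide intervals with 10 clinics, and unmeasured time-varying factors will remain.

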## 10.0 STUDY TIMELINE

| Study Activity                                | Year 1 |   |   |   | Year 2 |   |   |   | Year 3 |   |   |   |
|-----------------------------------------------|--------|---|---|---|--------|---|---|---|--------|---|---|---|
| IRB approvals; training of study personnel    | X      | X |   |   |        |   |   |   |        |   |   |   |
| Implementation of depression treatment models |        |   | X | X | X      | X | X | X | X      | X |   |   |
| Prospective cohort data collection            |        |   | X | X | X      | X | X | X | X      | X |   |   |
| Statistical analysis and write-up             |        |   |   |   |        |   | X | X | X      | X | X | X |

## 11.0 HUMAN SUBJECTS CONSIDERATIONS

### 11.1 Potential Risks to Participants

#### ***Side effects and interaction effects of antidepressant therapy***

The standard antidepressants to be used in this study include primarily fluoxetine and imipramine; amitriptyline is also available in Uganda but seldom used. The side effect profiles of these agents are thought to be relatively mild and infrequent, with the most common side effects including nausea, dry mouth, insomnia, headache, sexual side effects, somnolence, dizziness, sweating. These adverse events often dissipate as treatment continues, are reversible with treatment discontinuation, and rarely cause patients to decide to terminate therapy. It is also possible for antidepressants to have negative interaction effects with other medications being taken, including HIV antiretrovirals and anti-TB drugs, which can be manifested through physical symptoms and/or measures of immunosuppression (e.g., CD4). However, while interactions between these drugs are always conceptually possible, for the most part there is little evidence of significant interactions effects between antidepressants and HIV antiretrovirals. There is some data suggesting interaction effects between fluoxetine and HIV protease inhibitors, but very few patients are prescribed protease inhibitors at the study sites because NNRTI-based ART regimens (which do not contain a protease inhibitor) are the first line regimens in usual HIV care practice in Uganda and most of SSA. If drug interactions become evident, the primary care provider will consider dose modifications of the antidepressant or change in antidepressant.

### ***Psychological distress***

The participant may experience psychological distress while talking about issues raised during assessment interviews. A patient's depression could worsen, but this would not be expected to be a result of study participation.

### ***Confidentiality***

There is the potential for violation of participant confidentiality, but we believe the safeguards that we have integrated into the study methodology, as described in section E.5, will effectively limit these risks.

## **11.2 Protection Against Risk**

***Side effects and interaction effects of antidepressant therapy.*** If a participant receives antidepressant treatment, they will first receive a medical screen and psychiatric evaluation for appropriateness of antidepressant therapy as part of the depression treatment models prior to prescription of treatment by the primary care provider. At the sites implementing the task-shifting depression treatment model, the treatment response and side effects will be monitored by the DCM with a frequent visit schedule (treatment baseline, week 2, week 4, and then monthly thereafter until response, followed by every 3 months); in the standard, physician driven model, monitoring will be dependent on the primary care provider (who will receive training on use and monitoring of antidepressant therapy) as part of usual care. Patients will have 24-hour access to their primary care provider via phone for emergency contact. When side effects are reported, decisions related to dose reduction or discontinuation of treatment will be determined by the DCM and primary care provider, as outlined in the treatment model protocol. To monitor for possible interaction effects with HIV antiretrovirals, physical and adverse symptoms that are suspected to be possible interaction effects will be discussed between the treating providers and the site's supervising psychiatrist in their regular, ongoing supervision; also, CD4 count (and viral load, though it is rarely available) will also be monitored for potential interaction effects.

***Psychological Distress.*** Participants have the right to refuse to answer specific interview questions and can stop the interview at any time. If the patient's depression worsens and they are on antidepressants, changes to the medication dose or new antidepressant will be considered as indicated by the protocol, and the supervising psychiatrist will be consulted if needed. Some of the clinic sites have counselors, which could be asked to provide some supportive psychosocial counseling if desired by the patient.

***Confidentiality.*** To protect confidentiality, the following steps will be taken: All research data will be kept in locked file cabinets and will be available only to research staff directly involved in this project. Data will be identifiable only by study numbers and patient initials. HIV status will not appear along with any personal identifying information. The hand-held computer devices used to administer the computer-assisted personal interviews (at baseline and Months 6 and 12) will not collect any identifying information; only the study ID number and patient initials will be entered into these devices. The data on these hand-held computers will be password-protected and data will be uploaded to a study desktop computer on a daily basis. Personal information including subject's name, address, and phone number will be entered on a tracking form, stored separately from all research data, and kept in a locked file cabinet at the study site. Research interview data collected from the participants will be kept confidential and not be shared with the patient's physician or other clinic staff; the exception is the depression and psychiatric measures (PHQ-9, MINI, side effect measure), which will be shared with the patient's providers in order to optimize depression treatment. Patients will be informed of these conditions during the informed consent process.

### 11.3 Potential Benefits to Study Participants

All patient participants will be compensated 10,000 Ush (\$5 USD) for completing each primary research interview (baseline and Months 6 and 12); this is the standard amount used in Uganda for this type of interview and is recommended by the Uganda National Council for Science and Technology. Participants will not be compensated for visits that are just for depression treatment management.

### 11.4 Importance of the Knowledge to Be Gained

If we demonstrate that the task-shifting approach to depression treatment is feasible, effective and well incorporated into clinic systems, it will establish a model that addresses the human resource challenges to building the capacity for sustainable depression treatment. Findings will have implications not only for PLHA in SSA, but also other developing regions, non-HIV populations, and treatment of other diseases.

### 11.5 Data and Safety Monitoring Plan

**Potential Adverse Events.** We do not anticipate any medication-related adverse events beyond that of routine HIV and ART medical care, and use of antidepressant therapy. Patients who are treated with antidepressants will have been diagnosed with major depressive disorder and treated with standard antidepressant therapy. Only FDA approved antidepressant medications will be used. All patients will have been cleared medically for initiation of antidepressant therapy by their primary care provider. All patients will be assessed and monitored with regards to psychiatric symptoms and treatment side effects (including suicidality and potential interaction effects with ART) by the DCM on a frequent standardized schedule if at a site implementing the task-shifting treatment model, or as consistent with usual care at the sites implementing the standard physician driven treatment model. Antidepressant side effects are alleviated by dose reduction, and discontinuation if needed. Antidepressant side effects are reversible, and therefore terminate when the medication is discontinued.

*Protocol for suicidal ideation:* With the study population being depressed, some will express suicidal thoughts during the PHQ-9 assessment of depressive symptoms. In our current study, 27% of depressed patients expressed any suicidal ideation (14% had frequent thoughts) at treatment baseline. The DCM and physicians will be trained to implement the following protocol when patients report suicidal thoughts: an assessment will be made of the severity of the ideation, intent and means for carrying out any intent for suicide; this will then be followed with the activation of a plan to keep the patient safe, which could vary from more frequent contacts/visits, to establishing a suicide contract that includes 24-hour supervision of the patient by a community member, to inpatient admission for psychiatric care.

*Potential interaction effects between antidepressants and ART* will also be monitored in terms of both physical adverse events and also adverse changes in immunosuppression (e.g., CD4).

Participants whose psychiatric status significantly deteriorates, or who becomes a suicide risk, and who are in need of psychiatric hospitalization will be admitted to Mulago Hospital's Mental Health Unit. The supervising psychiatrists all have direct admitting privileges to Mulago and other hospitals located closer to the study sites, which lends itself well to affecting immediate psychiatric hospitalization and treatment to participants found to be suicidal or at risk for harming themselves or others.

In addition, a single, independent, clinical specialist in the treatment of depression (a psychiatrist from Makerere/Mulago Hospital) will serve as an independent monitor for the study. To allow effective monitoring, the independent monitor will be provided with periodic reports which include subject enrollment, subject retention, the number of patients who drop out of the study with reasons for dropping out, and a listing of all adverse events (AEs) that are plausibly

related to antidepressant therapy or other study procedures. Periodic reports will be provided to the independent monitor at six month intervals; however, AEs that are considered directly related to antidepressant therapy or other aspect of study participation will be reported immediately to the monitor, the IRBs, and NIH. After review of the periodic reports, the independent monitor may ask for clarification or additional information from the PI. After such information is provided, if requested, the independent monitor will make a recommendation regarding the continuation, modification, or termination of the study. All communications from the independent monitor will be shared with the IRBs and NIH.

**Data Integrity.** Identifying information including subject's name, address, and phone number will be entered on a tracking form, stored separately from all research data, and kept in a locked file cabinet at the study site. The hand-held computer devices used to administer the computer-assisted personal interviews (at baseline and Months 6 and 12) will not collect any identifying information; only the study ID number and patient initials will be entered into these devices. The data on these hand-held computers will be password-protected and data will be uploaded to a study desktop computer on a daily basis. All paper files are stored in locked file cabinets, and electronic files are stored in password-protected files. Furthermore, both paper and electronic files will be identified only by a participant's ID number. Identifying information linking participants to their study ID number will be retained in a locked cabinet.

Figure 1: Depression and Treatment Eligibility Assessment Protocol

[figure not shown]

Figure 2: Algorithm for Dose or Medication Changes

[figure not shown]

\* One increment: fluoxetine = 20 mg/day; imipramine = 50 mg/day

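### The independent monitor receives only adverse events judged related to treatment or the study, so suicide attempts and psychiatric admissions in patients not on antidepressants need not be reported

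*Protocol*

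**What the plan says.** Section 11.5 (Data and Safety Monitoring Plan) appoints one independent psychiatrist as monitor and sets out what that person is sent. The adverse event item in the six-monthly report is "a listing of all adverse events (AEs) that are plausibly" linked to the drug or to what the study does. The same report covers enrolment, retention and "the number of patients who drop out of the study with reasons for dropping out".

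Between reports there is one further route: "AEs that are considered directly related to antidepressant therapy or other aspect of study participation will be reported immediately to the monitor", and also to the IRBs and NIH.

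After reading a periodic report, "the independent monitor may ask for clarification or additional information from the PI". The monitor then recommends whether the study should continue, change or stop.

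Section 11.1, under Psychological distress, states: "A patient's depression could worsen, but this would not be expected to be a result of study participation".

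Section 11.5 expects suicidality in this population. It reports that in the investigators' current study "27% of depressed patients expressed any suicidal ideation (14% had frequent thoughts) at treatment baseline", and it describes how suicidal patients are to be assessed and, where needed, admitted. It does not connect those events to the monitor's reports.

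**The concern.** The trial compares two ways of detecting and treating depression. One harm that could differ between the arms is therefore what happens to patients whose depression is not picked up or treated. The monitor's adverse event information passes through a test of relatedness to the drug or the study, and that test suits side effects better than it suits the consequences of non-treatment.

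At stake is the basis for the monitor's recommendation. If serious psychiatric events in untreated patients are not on the listing, the monitor may be weighing drug-related events without the events that would count on the other side. This is a matter of safety oversight. It does not affect the primary endpoints or their analysis.

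**Working it through.** No figure in the protocol can be recomputed here. The check sets the safety passages side by side and follows an event through them.

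**1. The two adverse event routes (Section 11.5)**

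| Route | Filter | Seriousness criterion |
|---|---|---|
| Six-monthly listing | plausibly related to antidepressants or study procedures | none |
| Immediate report | directly related to antidepressants or study participation | none |

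Nothing in Sections 11.1 to 11.5 sends deaths, suicide attempts or psychiatric admissions to the monitor regardless of cause.

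**2. Following an event through the filter.** Take a patient who is not on antidepressants, makes a non-fatal suicide attempt and remains in the study.
- The event cannot be related to antidepressant therapy, because there is none.
- It is listed only if someone attributes it to study procedures or participation. The Psychological distress paragraph of Section 11.1 points away from that attribution.
- The patient has not dropped out, so the dropout item does not show it.

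A psychiatric admission follows the same path. A death differs: it may show up as lost retention or as a dropout with a reason, although the protocol does not say that deaths are counted that way.

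**3. Whether the filter acts equally in both arms.**
- *Uptake.* Section 9.1 assumes 30% uptake in the standard (clinical acumen) arm and expects a larger share in the task-shifting (protocolized) arm.
- *Monitoring.* Section 11.5 has side effects and suicidality followed on a frequent standard schedule by the depression care nurse in the task-shifting arm, and according to usual care in the standard arm.

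Both differences push the same way. Related events are more likely to occur and be recorded where more patients are treated and followed closely, while events in untreated patients are less likely to pass the filter.

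**4. Size of the group not on antidepressants.** The Study Overview gives 10 clinics, 5 per arm, with 100 to 150 patients each.
- Patients per arm: 5 × 100 = 500 to 5 × 150 = 750.
- Standard-arm patients not on antidepressants at 30% uptake: 0.70 × 500 = 350 to 0.70 × 750 = 525.

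This counts patients for whom the drug-related part of the filter cannot apply. It is not a count of missed events.

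**The case against.** The strongest reply is that the monitor is not blind to these events.

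- *Deaths.* Retention figures and dropout reasons are not filtered by relatedness, and the monitor can ask for more. This stands for deaths in part, and it is why they cannot be called excluded. It does not help with attempts and admissions in patients who stay enrolled, and a monitor has little reason to ask about an event never shown.
- *Wording of the filter.* The threshold for the listing is low, and study procedures or participation could be read to include screening and the care model itself. An attempt after a positive screen that was not followed up might then be judged related. This also stands: the exclusion is likely on the protocol's own reasoning but not certain. The Section 11.1 sentence is an expectation, not a reporting rule.
- *Arm comparison.* Section 11.5 does not say that the monitor sees data by arm. True, so no planned comparison is being distorted. The overall listing would still lean towards drug-related events.
- *Patient protection.* Care does not depend on this listing. Providers in both arms are trained in the suicide protocol (Section 11.5), supervisors are on call at all hours (Section 6.3), and research PHQ-9 results go to providers (Section 11.2). This limits the point to oversight.

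A reader might also infer that relatedness is judged by unmasked staff. The protocol does not say who makes the judgement, and the point does not need it.

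**Conclusion.** The gap is real and narrow. As written, Section 11.5 does not require non-fatal suicide attempts and psychiatric admissions in patients not on antidepressants who stay in the study to reach the monitor, and deaths may reach the monitor only indirectly. The tendency to show drug-related events more than harm from under-treatment rests on the uptake difference assumed in Section 9.1 and the monitoring difference described in Section 11.5.

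The size in events is unknown. Two inferences should be avoided:

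- Applying the 27% and 14% ideation rates to 1,000 to 1,500 patients gives 270 to 405 and 140 to 210. Those rates describe ideation at treatment baseline among depressed patients in another study. This trial enrols patients on a positive PHQ-2, and ideation at baseline is not an attempt, an admission or a death.
- The 350 to 525 patients without antidepressants are not all cases of depression left untreated. The 30% is a planning assumption, and under Section 6.1 a positive screen does not by itself establish major depression or eligibility for treatment.

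This is a worthwhile and inexpensive improvement to oversight, not a flaw that undermines the trial's results.

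**What to change.** Amend Section 11.5 so that the six-monthly report lists all deaths, suicide attempts and psychiatric hospitalisations by arm, regardless of judged attribution, in addition to the related adverse events already specified. State that these events are also sent to the monitor when they become known, rather than only when judged directly related.

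This changes what is reported and leaves clinical management as it is. The cost is somewhat longer listings, which will include some HIV deaths unrelated to the study. Little new data collection should be needed: supervising psychiatrists are the contact for suicide crises and hold admitting privileges, so many of these events should already be known to the study team.
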